## Abstract

**Background:**

Hypertension is the leading modifiable risk factor for cardiovascular disease, particularly in low- and middle-income countries (LMICs). Despite the effectiveness of pharmacological and non-pharmacological interventions, control rates remain low. Therefore, novel community-based strategies are needed for enhancing the detection, treatment, and control of hypertension. Our aim will be to implement and evaluate the results of a community-based strategy to reduce blood pressure (BP) levels in a LMIC.

**Methods:**

We describe the “Implementation, Integration, and Institutionalization of a Community-Based Care Program to Reduce Cardiovascular Risk in Santander” (RE-HOPE) study protocol. Adults aged ≥18 years, with *de novo* or uncontrolled hypertension, or with hypertension not participating in cardiovascular risk management programs, will be included. Individuals will be identified through active community screening. The intervention will consist of early identification of hypertension, enrolling participants in primary care institutions, and conducting follow-up home visits. These visits will include counseling on medication adherence and lifestyle modifications, as well as training for healthcare providers and community health workers (CHWs). Referrals to primary care providers and follow-up appointments will be coordinated by CHWs. The primary outcome will be change in BP levels from baseline to 12 months of follow-up.

**Results:**

We expect to generate evidence about implementation outcomes, such as feasibility and acceptability of community-based screening, the adoption of this approach by primary care centers and fidelity of activities developed by CHWs. In addition, the implementation of this model is anticipated to reduce the prevalence of uncontrolled hypertension and minimize barriers to healthcare access. It is also expected that this strategy facilitates the timely detection and monitoring, address institutionalization gaps, and ultimately reduce the long-term burden of hypertension.

**Conclusions:**

The RE-HOPE study will provide evidence on the effectiveness and implementation of a community-based hypertension control strategy integrated into primary care services. This strategy may serve as a replicable approach for improving hypertension control in low- and middle-income countries (LMICs).

## Introduction

Cardiovascular diseases are the leading cause of morbidity and mortality worldwide, with hypertension being the risk factor accounting for the highest population-attributable risk fraction (1, 2). Despite the availability of effective pharmacological treatments and non-pharmacological interventions, hypertension control remains suboptimal, contributing significantly to the global burden of disease and disability-adjusted life years (DALYs) (3). In the Americas, hypertension prevalence ranges from 18% to 60%, exceeding 40% in Caribbean countries. However, control rates remain low, 35% among women and 23% among men (4) In Colombia, the May Measurement Month 2019 campaign reported that 27.9% of participants had hypertension, 60% of whom were receiving treatment, yet only 38.4% had adequate blood pressure control (5). These figures have prompted the emergence of innovative strategies at both the individual and population levels to improve hypertension detection, management, and control, particularly in low- and middle-income countries (LMICs). Novel approaches include multidisciplinary care models involving non-physician health workers, continuous training of healthcare staff, task shifting, virtual care/telemedicine, the use of simplified diagnostic algorithms, and pharmacologic optimization through fixed-dose combination therapy (2, 6, 7). Indeed, multicomponent strategies that incorporate task-shifting and non-physician-led medication administration into standard care have demonstrated effectiveness in reducing systolic blood pressure by an average of 6.6 mmHg (95% CI: −9.0 to −4.2) (8). Community-based care models have also proven effective in managing hypertension in populations with limited healthcare access (9). Task-shifting interventions that engage community health workers (CHWs) enable them to perform key functions, such as screening, risk assessment, clinical follow-up, health education, self-care promotion, and adherence counseling. For example, the Heart Outcomes Prevention Evaluation 4 (HOPE-4) trial, a cluster-randomized community-based study, demonstrated that a CHWs-led intervention achieved systolic blood pressure control (<140 mmHg) in 69% of participants compared to 30% in the standard care group (*p* < 0.0001) (9). Such community-centered approaches are cost-effective for managing chronic diseases and offer a pathway to overcoming access barriers and promoting health equity. Community empowerment also has the potential to enhance health and well-being through strategies such as home visits, integration with medical consultations, and improved access to comprehensive healthcare services (10).

The “Implementation, Integration, and Institutionalization of a Community-Based Care Program to Reduce Cardiovascular Risk in Santander” (RE-HOPE) study will be developed to optimize community-level hypertension management by integrating CHWs into the processes of early detection, follow-up, and blood pressure control. The RE-HOPE model combines detection and referral mechanisms, structured health counseling, ongoing monitoring, and the use of simplified clinical algorithms to facilitate therapeutic decision-making and improve clinical outcomes.

Currently, cardiovascular risk programs at both the regional and national levels have gaps that limit their coverage. First, a high proportion of individuals with hypertension are unaware of their condition and therefore do not access cardiovascular risk programs; on the other hand, although some individuals with hypertension are aware of their disease, participation in institutional activities remains suboptimal. It is estimated that compliance with institutional programs is only around 60% (11). Additionally, among those already enrolled in cardiovascular risk programs, it is necessary to overcome some of the barriers identified by users in order to achieve hypertension control, including access to health services, coverage, education about the disease, and interaction with patients (12). The RE-HOPE model is designed to address these gaps by helping institutional cardiovascular risk programs increase their coverage. This will be achieved by strengthening patient engagement, reinforcing home-based health education, and improving continuity of care through more patient-centered strategies.

The distinguishing feature of the RE-HOPE study is the timely institutionalization of patients into cardiovascular risk management programs through structured coordination between community case detection and primary healthcare providers. We aim to develop an innovative and potentially scalable strategy that, if proven effective, may help close existing gaps in hypertension control in LMICs such as Colombia.

## Methods

### Study design

RE-HOPE will be a sequential mixed methods design study comprising two phases.

In the qualitative phase, we will conduct a study within the interpretive paradigm using a phenomenological design. Focus groups with stakeholders will be conducted using a semi-structured interview guide developed by the research team. Meetings will be held at participants' workplaces, and each session will be audio-recorded, transcribed verbatim, validated, and coded. Eligible professionals will be contacted by telephone and invited to participate voluntarily. Barriers to hypertension control identified during the formative phase, including difficulties in patient identification and challenges in coordination among health system actors affecting the delivery of cardiovascular risk programs, will be incorporated into the intervention design. Accordingly, the intervention seeks to reduce gaps in screening, improve awareness of hypertension, and strengthen healthcare professionals' knowledge of the diagnosis, treatment, and control of hypertension.

The second phase will consist of a quantitative study aimed at assessing the effectiveness of the implemented strategy. A single-arm intervention design will be used to evaluate longitudinal changes in blood pressure through within-participant comparisons of baseline and follow-up measurements.

The RE-HOPE study will be conducted in primary healthcare centers in Santander, Colombia. This manuscript describes the intervention protocol and follow-up procedures implemented by the community health team.

### Implementation general framework

The RE-HOPE study will be conducted within the general framework of the Exploration, Preparation, Implementation, and Sustainment (EPIS) model, which will guide the implementation process and inform the assessment of determinants influencing implementation. The EPIS model is a conceptual implementation framework that facilitates understanding of key contextual factors and their interactions throughout the implementation and sustainment phases. Specifically, EPIS comprises four stages: (1) exploration of the need for change; (2) preparation for intervention adoption; (3) intervention implementation; and (4) intervention sustainment over time (13). Across these four phases, the study will examine factors related to both the inner context (characteristics of healthcare institutions, providers, administrators, and staff) and the outer context (government agencies, communities, pharmacies outside clinics, and insurance companies/providers), as well as patient characteristics that may affect implementation. Table 1 presents the operationalization of the intervention components according to the EPIS framework, including contextual factors, implementation strategies, involved actors, implementation outcomes, and indicators. The RE-HOPE model will adapt a community-based intervention implemented by a working team comprising an operational coordinator, a data manager, community health workers (nursing assistants), community leaders, and healthcare professionals at primary care centers (PCCs). The roles of the team members are described in Table 2. The workload will be organized according to the identification and follow-up of individuals with hypertension in each community to which each nursing assistant is assigned (district or municipality). The individuals with hypertension may be served by one or more PCCs in each district or municipality.

**Table 1 T1:** Implementation of the RE-HOPE approach based on EPIS model.

EPIS phase	Context factor	Implementation strategy	Responsible actors	Implementation outcome	Indicator	Data source/time point
Exploration	Outer context	Engagement with community leaders and health authorities to introduce the RE-HOPE approach	Research team, community leaders, health authorities	Acceptability	Proportion of stakeholders reporting high acceptability of the intervention in the qualitative phase	Structured stakeholder survey; pre-implementation
	Inner context	Assessment of institutional readiness and implementation capacity in primary care centers	Research team, clinic managers	Feasibility	Number of primary care centers meeting readiness criteria	Readiness assessment checklist; pre-implementation
Preparation	Inner context	Training program for CHWs and nursing assistants on standardized BP measurement, counseling, referral procedures, and data entry	Research team, clinical trainers	Feasibility	Percentage of CHWs and nursing assistants completing certification training	Training attendance records; pre-implementation
	Inner context	Definition of operational workload for CHWs, including assignment of households and follow-up responsibilities	Research team, clinic managers	Feasibility	Mean number of households and participants assigned per CHW	Project operational records; pre-implementation
	Bridging factor	Coordination meetings between community teams and primary care cardiovascular risk programs	Research team, clinic managers	Adoption readiness	Number of coordination meetings conducted	Meeting minutes; pre-implementation
	Innovation factor	Development of standardized counseling materials and operational tools for home visits	Research team	Fidelity preparedness	Availability of standardized materials across participating clinics	Project documentation; pre-implementation
Implementation	Innovation factor	Community-based hypertension screening through door-to-door visits and outreach activities	CHWs, community leaders	Adoption	Number of individuals screened for hypertension per CHW	REDCap study database; implementation period
	Bridging factor	Referral pathway connecting community screening with cardiovascular risk programs in primary care	CHWs, primary care providers	Reach	Percentage of screened hypertensive individuals attending primary care appointment	Referral tracking system; implementation period
	Inner context	Delivery of structured home-based counseling sessions on hypertension management and lifestyle modification	CHWs	Fidelity	Proportion of planned home visits completed according to protocol	Visit checklists and REDCap records; implementation period
	Inner context	Monitoring and supervision of CHWs by nursing supervisors through periodic meetings and field visits	Nursing supervisors	Fidelity	Number of supervision meetings or field visits conducted per CHW	Supervision logs; implementation period
	Inner context	Monitoring of CHW workload during implementation	Nursing supervisors, research team	Feasibility	Average number of home visits conducted per CHW per month	Study database and supervision reports; implementation period
	Inner context	Follow-up visits at months 1, 3, 6, 9, and 12 including BP measurement and counseling	CHWs	Feasibility	Proportion of participants completing scheduled follow-up visits	Study database; implementation period
	Innovation factor	Health counseling sessions addressing medication adherence, physical activity, diet, alcohol reduction, smoking cessation, and stress management	CHWs	Acceptability	Participant satisfaction with counseling sessions	Participant satisfaction survey; implementation period
Sustainment	Inner context	Integration of RE-HOPE activities into existing cardiovascular risk management programs	Health authorities, clinic administrators	Sustainability	Inclusion of RE-HOPE protocol within institutional care pathways	Institutional documents; post-implementation
	Outer context	Evaluation of barriers and facilitators for long-term implementation and scale-up	Research team, health system stakeholders	Institutionalization	Identification of facilitators and barriers for future scale-up	Semi-structured interviews; post-implementation

BP, Blood pressure; CWHs, Community Health Workers.

**Table 2 T2:** Role of team members.

Members	Function	Activities
Nurse, Operational Coordinator	Management in the territory	Coordinate the deployment of nursing assistants and community leaders.
		Liaise with PCCs and maintain communication.
		Conduct training for nursing assistants, community leaders, and health workers at PCCs.
		Supervise the activities of nursing assistants and the health counselling.
		Supervise data collection.
Community Health Workers-Nursing assistant	Monitoring of hypertensive individuals. Data collection	Conduct home visits, with standardized blood pressure measurements.
	Health counselling	Offer health counselling according to individual educational needs.
		Fill out follow-up forms.
		Report any new developments or alarming situation.
		Provide reminders.
Data manager	Systematization of data	Supervise data collection.
		Centralize data
		Generate reports.
Community leaders.	Liaise with community.	Facilitate contact between nursing assistants and people in the community.
		Carry out logistical tasks to enable home visits to take place.
Health workers in PCC	Institutionalize the person with hypertension	Schedule medical appointments.
		Provide reminders.
		Enroll individuals in institutional cardiovascular risk programs.
		Prescribe antihypertensive medication.

PCC, Primary Care Center

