### Population and sample

Adults aged ≥18 years be selected through convenience sampling from the community based on the following criteria: a) newly diagnosed hypertension (defined as blood pressure ≥140/90 mmHg); b) uncontrolled hypertension (defined as blood pressure ≥140 mmHg in individuals with a previous diagnosis of hypertension or who are currently on antihypertensive treatment); and/or c) known hypertensive individuals not regularly attending cardiovascular risk management programs at primary care centers. Exclusion criteria include established cardiovascular disease (e.g., coronary artery disease, myocardial infarction, heart failure, arrhythmias, cardiomyopathies, peripheral arterial disease, stroke or transient ischemic attack, diabetes mellitus with macrovascular complications, or history of invasive cardiovascular procedures), chronic kidney disease requiring dialysis, intolerance to antihypertensive medications, and resistant or secondary hypertension. The exclusion of these people was based on the fact that these pathologies require individualized and specialized management at high levels of care, which exceeds the capabilities of a community-based strategy.

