### Implementation outcomes

Implementation fidelity will be assessed to determine whether home visits and planned CHW-led activities were carried out in accordance with the protocol. Coverage will be measured as the proportion of the target population reached, and acceptability will be evaluated from the perspectives of participants, CHWs, and healthcare personnel. Operational feasibility will be examined by identifying logistical, administrative, and contextual barriers and facilitators. Finally, the medium- and long-term sustainability of the strategy, as well as its scalability to other settings, will be explored to support its integration into the primary healthcare system (Table 1).

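### The Adoption indicator counts people screened per CHW, not uptake by primary care centers, and Table 1 has no indicator for coverage as the article defines it

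*Protocol article*

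**What the plan says.** The protocol article's Abstract (Results) lists, among the evidence the study expects to generate, "the adoption of this approach by primary care centers and fidelity of activities developed by CHWs". The section Implementation general framework says that Table 1 sets out the implementation outcomes and their indicators.

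In Table 1, Implementation phase:

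- **Adoption** appears in one row. The strategy is "Community-based hypertension screening through door-to-door visits and outreach activities", the responsible actors are CHWs and community leaders, the indicator is "Number of individuals screened for hypertension per CHW", and the source is the REDCap database.
- **Reach** belongs to the referral pathway from community screening to the cardiovascular risk programs. Its indicator is "Percentage of screened hypertensive individuals attending primary care appointment", taken from the referral tracking system.

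The section Implementation outcomes states: "Coverage will be measured as the proportion of the target population reached". Its paragraph closes with a reference to Table 1, which contains no row called coverage.

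**The concern.** Adoption by centers is a statement about centers: how many of those that could take up the program did so. A count of people screened per CHW is a statement about how busy the project's own field staff were. It can be high while no center changes anything, and low while every center enrols whoever is sent.

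Coverage is a statement about a population, including people whom screening never found. Reach as written starts after screening, so the people missed by screening cannot affect it.

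This matters because implementation and institutionalization are in the study's title. The Introduction names timely entry into institutional programs as the distinguishing feature and presents the model as a way to widen those programs' coverage. Followed literally, Table 1 would allow favourable statements on adoption, and on coverage if Reach is used for it, from data that bear on neither.

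**Working it through.** The documents give no target or expected value for adoption or coverage, so there is no plan figure to reproduce. The check compares each stated construct with its indicator by unit and denominator, then tests whether one could stand in for the other. **All numbers below are assumed, for illustration only.**

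**1. Adoption: units**

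| | Abstract (Results) | Table 1, Adoption row |
|---|---|---|
| Who adopts or acts | Primary care centers | CHWs, community leaders |
| Numerator | Centers taking up the approach | People screened |
| Denominator | Centers that could take it up | CHWs |

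The two share no term.

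**2. Adoption: does the indicator respond to center uptake?**

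Indicator = people screened / CHWs. Assume 4,000 screened, 20 CHWs and 20 centers.

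- 2 of 20 centers adopt (2/20 = 10%): indicator = 4,000/20 = 200.
- 20 of 20 centers adopt (20/20 = 100%): indicator = 4,000/20 = 200.

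Neither input involves a center, so the result is the same for any choice of numbers.

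**3. Adoption: do other Table 1 rows fill the gap?**

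- "Number of primary care centers meeting readiness criteria" is labelled Feasibility and taken before implementation. It measures readiness.
- "Number of coordination meetings conducted" is labelled Adoption readiness and also taken before implementation. It counts meetings held.
- The Sustainability row asks whether the RE-HOPE protocol has been written into institutional care pathways. This does concern institutional uptake, but it is assessed only after implementation and under another label.

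**4. Coverage against Reach**

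- Coverage (Implementation outcomes) = people reached / target population.
- Reach (Table 1) = hypertensives attending an appointment / hypertensives screened.

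If reached means attending, the target is all hypertensives in the area and every attender came through screening, then

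coverage = (hypertensives screened / target hypertensives) × Reach.

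Holding Reach at 80%:

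| Share of target screened | Coverage = share × 0.80 |
|---|---|
| 10% | 8% |
| 30% | 24% |
| 60% | 48% |
| 100% | 80% |

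Reach equals coverage only when everyone in the target has been screened. If reached instead means screened, coverage is the left-hand column and Reach says nothing about it.

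**The case against.** The strongest reply is that this is largely a matter of labels. Institutional uptake is not ignored: the Sustainability row records it, readiness is checked beforehand, and the secondary outcomes include the share of people with hypertension not enrolled in a risk program. That stands in part. Center uptake is mislabelled and late, not wholly unmeasured. But the secondary outcome is counted per person and does not show how many centers took the program up, and the row actually called Adoption remains uninformative about centers.

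A second reply is that the article never says Reach is the coverage measure. The reference to Table 1 closes a sentence on sustainability and scalability and may not extend to coverage. That is fair. What remains is that coverage is defined in the text, has no indicator in the table that operationalizes the outcomes, and has a near neighbour that could easily be reported in its place.

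Three stronger readings are tempting and are not supported:

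- *That coverage cannot be computed because participants will "be selected through convenience sampling from the community".* The way the cohort is sampled does not settle the denominator. It could come from an external count or from the households assigned to each CHW, which Table 1 records as a workload item. A condensed article may leave that source to the full protocol.
- *That screening at primary care facilities inflates attendance by some amount.* The documents give neither the mix of venues nor attendance by venue. The Reach row concerns community screening, and being found at a facility is not the same as attending the scheduled appointment with the assigned provider.
- *That acceptability is mis-measured.* Implementation outcomes assesses it from the perspectives of participants, CHWs and healthcare staff, and the stakeholder survey rates the intervention, of which screening is a part.

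**Conclusion.** The point holds in two specific respects. First, the sole Adoption indicator carries no information on adoption by primary care centers, which is what the Abstract promises. This follows from the definitions and needs no assumed figures. Second, coverage as defined in Implementation outcomes has no indicator in Table 1, and Reach cannot substitute for it. In the illustration a Reach of 80% goes with coverage of 8% to 80%, and that range rests entirely on the assumed share of the target population screened.

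The consequence is limited to how the implementation results can be interpreted. The primary outcome, the sample size and the effectiveness models do not use these indicators. The change is worth making because the study could otherwise not answer, during implementation, a question it sets itself, and the correction is cheap.

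**What to change.** In Table 1:

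1. Relabel people screened per CHW as screening output or workload.
2. Make the Adoption indicator the number of primary care centers that enrol referred participants in their cardiovascular risk program, divided by the centers that received referrals (or were approached; state which). Take it from the referral tracking system. Report beside it, for each center, the proportion of referred participants enrolled, so that one enrolment does not count as full adoption.
3. Rename Reach as referral completion, with all confirmed hypertensives as denominator.

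In Implementation outcomes, either name the target population for coverage and the source of its size, or make clear that referral completion will not be reported as coverage. Redefining coverage as referral completion is not a solution, because it would write the confusion into the plan.

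The cost is rewording plus a tabulation by center of referral data already planned. The adoption and coverage figures may look less favourable than the current indicators would.
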